### Design of trial

2.2

The trial is a 4-group, parallel, RCT, which has been registered at www.clinicaltrials.gov (Identifier: NCT02468531). By performing 4 2-way comparisons, we will test differences between groups. Patients will be randomized in a 1:1:1:1 ratio. Blinding will be performed for patients, post intervention assessors, statisticians, and investigators.

The null hypothesis for this trial is that there is no difference in protection effects between nitrogen and xenon in patients with postoperative oxygen impairment. The patients who receive nitrogen are the control group in this comparison. If this null hypothesis is rejected, then inhaled xenon may be an effective treatment. If this null hypothesis is not rejected, then inhaled xenon may be ineffective.

However, there is also a need to understand how potential treatment differences are achieved, and/or if different concentrations of inhaled xenon produce similar effects. Further comparisons, including the use of a control intervention, can provide this information.

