#### Sample size calculation

3.4.2

The sample size calculation is based on the primary outcome measure, which is the variable of OI at perioperative period. Currently, there is no established minimal clinically important difference (MCID) for the OI. Based on previous study,^[17]^ an approximation to the MCID could be viewed as 38 mm Hg, the standard deviation (SD) of a single OI observation as 70 mm Hg, and the auto-correlation as 0.5. With a 5% (2-sided) type I error rate, based on preliminary experiments, 36 patients per treatment group are necessary, and the power was 0.80048. Assuming a 10% dropout rate, the final sample size will be 160 patients (40 patients/group) (Table 2). (Power Analysis and Sample Size, PASS V11.0, NCSS, LLC; Kaysville, UT).

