#### Analysis of endpoints

3.4.3

The statistical analysis of the study is the responsibility of the trial statistician. Baseline data will be compared to determine whether or not there are any clinically important differences between treatment and control groups that have occurred by chance. The analysis will be performed by SPSS statistical software (SPSS for Windows, V.18.0; Chicago, IL).

All statistical testing will be performed at the 2-sided 5% significance level, and 95% confidence intervals will be presented where appropriate. For all analyses, the appropriate model assumptions were verified, and alternative methods used if more appropriate. Prior to any analysis, any missing data patterns will be investigated, the reasons for missing data obtained and summarized where possible. The primary analysis, such as OI, inflammatory cytokines, and ROS, will be conducted on the repetitive measurement and analysis of variance. The intubation time will be summarized descriptively using median, interquartile ranges and ranges overall, as well as by treatment arm. Complications between the trial arms will be compared in terms of frequency and severity. Cross-tabulations will be generated to relate complications to treatment, and chi-squared tests will be used to assess the significance of the association. A receiver operating characteristic (ROC) curve will be used to test discrimination of the treatment model. A *P* value <.05 will be considered statistically significant.

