### Interpretation

4.3

The importance of highlighting potential outcomes and clinical implications has been shown by the development of this trial. If each concentration of xenon-treatment is shown to be no more effective than nitrogen-control, then the continued use of xenon for this condition and in a wider context should be terminated. Conversely, if 50% xenon (or 75% xenon or 100% xenon) is shown to be an effective treatment, then the current xenon-treatment for the procedure should be encouraged. If 100% xenon is more effective than 50% xenon, then it will have been confirmed that the effectiveness of xenon is based on concentration. If a comparison of 100% xenon with 50% xenon demonstrates no difference in primary outcome, then there are health care economic implications, and a cost utility analysis will be performed for future procedures.

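### The 100%-versus-50% xenon conclusion in section 4.3 rests on a non-significant difference test, with no similarity margin and no explicit link to the nitrogen comparison

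*Protocol article*

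**What the plan says.** The protocol article makes dose similarity one of the trial's questions. Section 2.2 (Design of trial) wants to know "if different concentrations of inhaled xenon produce similar effects".

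Section 4.3 (Interpretation) sets out how results will be read, in this order:

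- Against nitrogen: "If each concentration of xenon-treatment is shown to be no more effective than nitrogen-control, then the continued use of xenon for this condition" is to be terminated. Conversely, if a concentration proves effective, its use is to be encouraged.
- Between doses, if a difference is found: "If 100% xenon is more effective than 50% xenon, then it will have been confirmed that the effectiveness of xenon is based on concentration".
- Between doses, if none is found: "If a comparison of 100% xenon with 50% xenon demonstrates no difference in primary outcome, then there are health care economic implications". The stated follow-up is a cost utility analysis.

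Section 3.4.3 (Analysis of endpoints) gives the inferential framework: "All statistical testing will be performed at the 2-sided 5% significance level". The same sentence adds that 95% confidence intervals will be shown where appropriate. No equivalence or non-inferiority margin appears anywhere. Section 3.4.2 (Sample size calculation) sizes the trial for one difference only: "an approximation to the MCID could be viewed as 38 mm Hg".

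**The concern.** A difference test can show a difference; it cannot show that there is none. With no margin and no interval criterion, the only operational meaning of the last rule is P ≥ .05 for 100% versus 50% xenon. Section 2.2 reads non-rejection in a similar way for the nitrogen comparison: "If this null hypothesis is not rejected, then inhaled xenon may be ineffective".

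Two things are at stake. First, the article could draw a cost argument between doses, which makes sense only if their effects are comparable, from data that do not exclude a difference as large as its own approximate MCID. Second, the dose sentence does not say that either dose must first have been shown better than nitrogen. Two ineffective doses satisfy it as readily as two equally effective ones.

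**Working it through.** **Inputs.** From section 3.4.2: difference 38 mm Hg, SD of a single oxygenation index (OI) value 70 mm Hg, autocorrelation 0.5, two-sided 5%, 36 per group, power 0.80048, 40 per group after 10% dropout. From section 2.4.1: three OI measurements. Section 4.2 allows dropout up to 15%, so 40 × 0.85 = 34 evaluable per group is the low end.

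**Step 1: reproduce the stated size.** Take the mean of three OI values with equal correlation 0.5.

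- SD of the mean = 70 × √((1 + 2 × 0.5)/3) = 57.15.
- n = 2 × 57.15² × (1.960 + 0.842)² / 38² = 35.5, so 36 per group.
- SE at 36 per group = 57.15 × √(2/36) = 13.47. Power is 0.805 (normal) or 0.800 (t, error pooled over four arms, 140 df), against 0.80048 stated.
- 36/0.90 = 40.

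The plan's figures reproduce, so this model is used below.

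**Step 2: how often the rule fires when the doses differ.** Firing rate = 1 − power of the two-sided 5% test (noncentral t, noncentrality = gap/SE). Half-width = t × SE. The 19 mm Hg gap is half of 38 and is my assumption.

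| Evaluable per arm | SE | 95% CI half-width | Fires, true gap 38 | Fires, true gap 19 |
|---|---|---|---|---|
| 34 | 13.86 | 27.4 | 22% | 73% |
| 36 | 13.47 | 26.6 | 20–21% | 71% |
| 40 | 12.78 | 25.2 | 16% | 68–69% |

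**Step 3: what a no-difference result would still allow.** With a true gap of 19 and half-width h, the rule fires with probability p ≈ Φ((h − 19)/SE), and the 95% CI reaches 38 when the estimate exceeds 38 − h. Because 19 is half of 38, the conditional probability is (2p − 1)/p.

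- 36 per arm: p = Φ(0.567) = 0.714, giving 60%.
- 40 per arm: p = Φ(0.489) = 0.687, giving 54%.

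**Step 4: no xenon effect.** The dose rule fires in 95% of trials, which is simply 1 − 0.05. In simulation at 36 and 40 per arm, no concentration beats nitrogen in about 94% of trials, and the termination rule and the dose rule fire together in about 90%.

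**Step 5: sensitivity to the analysis model.** For a 19 mm Hg gap at 36 and 40 per arm, the firing rate is 74% and 72% using the mean of the two postoperative values, 79% and 78% at a single time point, and 64% and 60% with baseline adjustment. None of these reproduces the stated power at 36 per group.

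**The case against.** The best defence has four parts.

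- **Order of the paragraph.** Section 4.3 opens with the nitrogen comparison, and the dose sentences come afterwards. A natural reading is that they apply only once xenon has been found effective. This largely stands. A reader might infer that the plan ignores nitrogen when comparing doses, or treat the 95% firing rate under no effect as a defect in itself. The documents support neither. The nitrogen rule is in the same paragraph, and 95% is what any 5% test gives under its null. What remains is that the link is left unstated, so the text as written allows both rules to apply to the same result.
- **Modest consequence.** A reader might infer that the trial will declare the doses equal or interchangeable. The text does not say so. It speaks of economic implications and a later analysis, and the article leaves the choice of concentration to future trials. This limits the harm, but a cost argument between doses still presupposes comparable effect.
- **The 19 mm Hg gap.** No figure in the documents supports it, nor the claim that a gap between active doses must be smaller than 38. At 38 mm Hg the firing rate is about the planned type II error. That is fair, but a type II error of that size still does not demonstrate absence of a difference.
- **Condensed article.** Margins are commonly left to an analysis plan, and section 3.4.3 does promise confidence intervals where appropriate. But the article itself fixes the rule and its consequence, and does not say the interval will decide it.

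**Conclusion.** The concern holds as a fault of inference and of linkage, not of the primary nitrogen comparisons, which are unaffected. As written, a non-significant 100%-versus-50% result is enough for the economic conclusion.

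Under the plan's own sizing model this happens in about 16–21% of trials (36 to 40 per arm) when the doses truly differ by 38 mm Hg. It happens in about 68–73% (34 to 40 per arm) when they differ by an assumed 19 mm Hg. These figures rest on SD 70, equal correlation 0.5 and the mean of three OI values; other reasonable analyses give 60–79% for the 19 mm Hg gap. The size of the problem therefore depends on the assumed gap, but its existence does not: no value of P ≥ .05 can demonstrate similarity without a margin. The revision should be made, and it needs no change to the design.

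**What to change.** Reword the dose-similarity sentence in section 4.3 and carry it into the analysis plan:

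- (a) Draw the similarity and cost conclusion only if 50% and 100% xenon have each been shown superior to nitrogen on OI.
- (b) Base it on the confidence interval for the 100%-minus-50% OI difference lying wholly within a pre-stated margin no wider than 38 mm Hg. Otherwise report the estimate and interval as inconclusive on dose, with no economic claim.
- (c) State that the expected 95% CI half-width is about 25–27 mm Hg. Do not state a fixed difference that cannot be ruled out, because what is excluded depends on the observed estimate.

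The sponsor should justify the margin. At the widest permitted value, a true 19 mm Hg gap would still pass in about 27–31% of trials: Φ((38 − 26.6 − 19)/13.47) − Φ((−38 + 26.6 − 19)/13.47) = 0.285 − 0.012 at 36 per arm, and 0.313 − 0.006 at 40 with h = 25.2 and SE = 12.78.

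**Cost.** No patients and no new data, but fewer similarity claims. With truly equal doses the chance that the interval lies within ±38 is 2Φ((38 − h)/SE) − 1. For the 95% CI this is about 60% at 36 per arm (h = 26.6) and 68% at 40 (h = 25.2). With a 90% CI, as for two one-sided tests, it is about 76–81%. Adding condition (a), with both doses truly 38 mm Hg better than nitrogen, lowers the 95% CI figure to about 47–55% by simulation.

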### Dissemination

4.4

Data collection will be completed by mid- or late-2018. Data analysis will start immediately after data monitoring completed. Publications will be prepared for submission in mid-2019. The results of the trial will be published according to the CONSORT statement. Dissemination of results will focus on publications in peer-reviewed journals, and presentations at national/international cardiology surgery or anesthesiology meetings to have widespread dissemination.
